## Methods/design

### Study design

This study is a two-arm parallel, patient-assessor blinded, non-penetrating sham-controlled randomized clinical trial. The trial will be performed in the Korean Medicine Hospital of Kyung Hee University at Gangdong in Korea in accordance with the Declaration of Helsinki and the Guidelines for Good Clinical Practice. This protocol was registered with the US National Institutes of Health Clinical Trials registry. Eligible participants will be randomly allocated into one of two groups (the real acupuncture treatment group or the sham acupuncture control group) in a 1:1 allocation ratio, blinded to the group allocation, and will receive treatment for 6 weeks (Fig. 1). The outcome assessment and the statistical analysis will be performed by professionals blinded to the assignment of participants to either the real or sham acupuncture.

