### Outcome

#### Primary outcome measurement

The primary outcome measure is the serum cholesterol levels including HDL cholesterol, LDL cholesterol, and triglyceride (TG) levels. Peripheral blood will be drawn from the antecubital veins of the subjects in the real and sham acupuncture groups at baseline (visit 2) and endpoint (visit 14: within 3 days after completion of the 6-week treatment) after a 10–12 hour overnight fast. Blood samples will be collected in serum-separating tubes (5 mL), sodium fluoride tubes (3 mL), and EDTA-coated tubes (2 mL) and will be centrifuged at 3,000 rpm for 10 minutes to separate either serum or plasma depending on the requirement of the analysis. Aliquots of plasma and sera will be obtained, and serum-separating tubes and sodium fluoride tubes will be stored at 2 to 10 °C while EDTA-coated tubes will be stored at −80 °C for further analysis. Analysis of TG, HDL cholesterol, LDL cholesterol, free fatty acids, glucose, hs-CRP, and insulin will be performed by an outsourcing laboratory (EOne Laboratories, Incheon, South Korea), and analysis of other lipids, amino acids, and carnitines will be commissioned to the research laboratory of the College of Pharmacy, Hanyang University in Korea.

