### Sample size

The following hypotheses are related to the differences between the treatment and control groups:$$ {H}_0:{\upmu}_{\mathrm{c}}={\upmu}_{\mathrm{t}} $$$$ {H}_1:{\upmu}_{\mathrm{c}}\ne {\upmu}_{\mathrm{t}} $$

where μ_t_ is the mean TG level in the real acupuncture treatment group and μ_c_ is the mean TG level in the sham acupuncture control group at endpoint.

Referring to a previous study [18], the researchers expect the mean difference will be 32.5 with a standard deviation of 56.907 between the two groups.

For the mean comparison method of the two-sample *t*-test model, this study will use a level of significance of α = 0.05 and a power of 1-β = 0.80 and the following two-sided test:$$ N=\frac{2\times {\left({\mathrm{Z}}_{\upalpha}+{\mathrm{Z}}_{\upbeta}\right)}^2\times {\upsigma}^2}{\updelta^2}=\frac{2\times {\left(1.96+0.84\right)}^2\times {56.907}^2}{32.5^2}=48.07\approx 48 $$

For equal allocation of the two groups, the total sample size required when considering a dropout rate of 20 % is 120 subjects with 60 subjects in each group.

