### Statistical analysis

All analyses will be performed using SPSS for Windows (version 18.0; IBM Corp., Armonk, NY, USA) and a significance level set at 0.05 by a statistician blinded to the allocation of groups. Statistical analysis will be conducted using the principles of the intention-to-treat (ITT) [34] and the per-protocol (PP) [35] analyses. We will apply the last observation carried forward (LOCF) analysis for ITT analysis.

The two-sample *t*-test for quantitative data and the chi-square test for qualitative data will be performed to test homogeneity of the baseline characteristics between the two groups. Analysis of covariance (ANCOVA) will be used for adjustment of baseline characteristics if there is a possibility of covariance. The two-sample *t*-test will be used to compare the primary and secondary variables of the two groups between baseline and endpoint. Repeated measure analysis of variance (ANOVA) will be performed for the different time point assessments between groups and interaction between groups and observed time. A mixed model approach will also be used if necessary.

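### The unadjusted raw-scale t-test is valid but inefficient: fix baseline-adjusted ANCOVA as the primary comparison, on the log scale for triglycerides

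*Protocol article*

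**What the plan says.** All references are to the protocol article.

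- **Primary outcome measurement:** "The primary outcome measure is the serum cholesterol levels including HDL cholesterol, LDL cholesterol, and triglyceride (TG) levels". Blood is drawn at visit 2 (baseline) and visit 14 (endpoint), so each woman should supply both values.
- **Sample size:** the hypothesis concerns endpoint means; the treatment-arm parameter "is the mean TG level in the real acupuncture treatment group". The planning figures are on the raw scale: "the researchers expect the mean difference will be 32.5 with a standard deviation of 56.907 between the two groups". The test is two-sided, with "a level of significance of α = 0.05 and a power of 1-β = 0.80". The total, after allowing for 20% dropout, "is 120 subjects with 60 subjects in each group".
- **Statistical analysis:** the two-sample t-test "will be used to compare the primary and secondary variables of the two groups between baseline and endpoint". ANCOVA is mentioned only conditionally, for the case where covariance with baseline characteristics is thought possible. Repeated-measures ANOVA covers outcomes with several time points, and a mixed model is held in reserve. No transformation or rank-based method is mentioned.

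**The concern.** Two features of the stated comparison cost precision.

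1. The baseline value of each primary lipid is measured but has no assured place in the primary comparison. The wording does not settle whether the t-test is applied to endpoint values, as the Sample size hypothesis suggests, or to changes from baseline. Neither uses the baseline as well as a covariate does.
2. TG cannot be negative, the eligibility criteria set no lipid limit, and the planning SD is 56.907. If mean TG is modest relative to that SD, the distribution is probably right-skewed and the raw scale is not the most efficient one.

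At stake is the power to detect an effect on a primary outcome with data that the trial collects anyway.

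**Working it through.** **Inputs from the article.** Difference 32.5, SD 56.907, two-sided α 0.05, power 0.80, allocation 1:1, 20% dropout.

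**Inputs assumed.** The article gives no mean TG, no distribution and no baseline–endpoint correlation. I take a mean of 110 to 180 in the same unit as the SD, a log-normal shape, and a correlation of 0.5 between log baseline and log endpoint.

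**Step 1: the plan's own figure.** n = 2 × (1.96 + 0.84)² × 56.907² / 32.5² = 48.07, taken as 48 per group. 48 / (1 − 0.20) = 60 per group, 120 in total. Both figures reproduce. Power is 79.9% at 48 and 87.9% at 60 per group.

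**Step 2: what the baseline covariate gives, with no assumption about skew.** Relative to an endpoint comparison, the variance factor is 2(1 − ρ) for change and 1 − ρ² for ANCOVA. At ρ = 0.5 these are 1.00 and 0.75.

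- Standard error of the endpoint comparison: 56.907 × √(2/48) = 11.616.
- Endpoint (or change): 32.5 / 11.616 = 2.798; power ≈ Φ(2.798 − 1.96) = 80%.
- ANCOVA: 2.798 / √0.75 = 3.231; power ≈ Φ(3.231 − 1.96) = 90%.

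**Step 3: is skew plausible?** A normal model with SD 56.907 puts this share of women below 30 units, Φ((30 − mean)/56.907):

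| Assumed mean | Share below 30 |
|---|---|
| 110 | 8.0% |
| 130 | 3.9% |
| 150 | 1.7% |
| 180 | 0.4% |

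The hint of skew is clear at the low end of the range and fades at the high end. The cut at 30 is arbitrary.

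**Step 4: raw against log.** Simulated power at 48 per arm. SD is 56.907 at baseline and in the sham arm, and the effect is proportional and equal to a 32.5 fall. Ranges run over means 110 to 180 and carry about one point of simulation error.

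| Comparison | Raw | Log |
|---|---|---|
| Endpoint t-test | 86–91% | 88–94% |
| Change t-test | 80–82% | 87–94% |
| ANCOVA on baseline | 93–96% | 95–98% |

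The raw endpoint figures exceed 80% because a proportional fall also shrinks the SD in the active arm. Adding the baseline covariate on the raw scale raises power by about 5–7 points over the endpoint test and about 12–14 over the change test. Logging then adds about 2.

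**Step 5: sensitivity.**

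- Pooled endpoint SD held at 56.907, endpoint t-test, proportional effect: 81% raw to 87% log at a sham mean of 110, narrowing to 80% and 81% at 250.
- Same setting with a constant shift, or equal raw SDs in both arms: the log gain is larger, about 5 to 18 points.
- Smaller effect (15% fall, mean 130, correlation 0.6): change 47% raw and 56% log; ANCOVA 60% raw and 65% log.
- Type I error of the raw t-test under log-normal data: 4.9–5.1%.

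**The case against.** The strongest reply is that nothing here is wrong. Hypothesis, sample size and test all sit on the raw scale and agree with one another; the test holds its type I error; and the sample size was built on the raw SD. That stands in full. A reader might infer that the planned power is lost, or that a few women with high TG will decide the result. The documents support neither: the 80% is computed for the raw t-test, and they contain no distributional data.

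A second reply is that transformation rules are usually left to an SAP, which is not shown. For hs-CRP, insulin, the metabolites and the physical activity questionnaire this stands: use of the raw scale is inferred from silence, and their skewness is a general expectation, not something the article shows. It does not stand for TG, where the article itself fixes the raw mean as the target and the t-test as the method.

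A third reply is that a log analysis is not free. That is right: it replaces the difference in arithmetic means by a ratio of geometric means. Exact log-normality is also the case that favours logs. Finally, the argument for logging says nothing about HDL and LDL cholesterol, which are also primary; for them only the baseline covariate is at issue.

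**Conclusion.** The point holds as a cheap efficiency improvement, not as an error. The comparison as stated is valid and its 80% power is intact. The main gain lies in making baseline adjustment the rule: at a correlation of 0.5, power rises from about 80% to about 90% on the plan's own figures without any assumption of skew, and to 93–96% in the log-normal scenarios. Logging TG adds about 2 points to ANCOVA and about 2–3 points to the endpoint t-test in the main scenarios. It adds more (about 6–12 points) only if raw change scores are what is tested, and the article does not settle that.

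All of this rests on an assumed correlation. The log-scale figures also rest on an assumed mean TG, a log-normal shape and a proportional effect. A higher correlation would increase the gain from ANCOVA over the endpoint test, and a higher mean TG would reduce the gain from logging.

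**What to change.** - State that the primary comparison of each lipid is ANCOVA of the endpoint value on treatment group with the baseline value as covariate, unconditionally. This replaces the unadjusted t-test and removes the doubt over endpoint or change.
- For TG, analyse the natural log of the endpoint value with log baseline as covariate. Report the ratio of geometric means with a 95% confidence interval. Do the same for other strictly positive markers expected to be skewed, such as hs-CRP and insulin, unless the SAP already provides for it.
- Keep the raw-scale TG difference as a sensitivity analysis, so that the contrast in the Sample size section is still reported.
- Settle this before unblinding, because choosing the scale or the covariate after seeing the results would be an open analytic choice on a primary outcome.

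**Cost.** Wording only: the baseline and endpoint samples are already scheduled at visits 2 and 14, and no participants or visits are added. The real downside is that the TG estimand becomes a ratio, so the hypothesis in the Sample size section must be restated on that scale. The planned 60 per group can stay.

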#### Secondary outcome measurements

Body weight, body fat mass, and muscle mass will be measured by bioelectrical impedance analysis using a body composition analyzer (InBody 720, InBody Co., Ltd., Seoul, Korea) and waist and hip circumference will be measured three times by the same observer according to the World Health Organization (WHO) method [23], midpoint between the lower end of the rib cage and top of the iliac crest in a standing position, which is usually 3 cm above the anterior superior iliac spine and the widest portion of the buttocks at baseline, at 2, 3, 4, 5, and 6 weeks and endpoint (visits 2, 4, 6, 8, 10, 12, 14).

Serum metabolic profile including the following will be determined: phospholipids, fatty acids, valine, tyrosine, leucine, glycine, alanine, glutamic acid, histidine, pipecolic acid, L-carnitine, acetylcarnitine, propionylcarnitine, butyrylcarnitine, isovalerylcarnitine, hexanoylcarnitine, ocatanoylcarnitine, decanoylcarnitine, dodecanoylcarnitine, tetradeconoylcarnitine, hexadecanoylcarnitine, and octadecanoylcarnitine. Glucose, hs-CRP, and insulin will also be measured (visits 2, 14).

The International Physical Activity Questionnaire (IPAQ) [24] will be used to estimate physical activities at baseline and endpoint (visits 2, 14). IPAQ is a seven-item instrument consisting of six questions that participants answer to record the number of days (frequency) and the number of minutes per day (duration) of their participation in all types of vigorous or moderate physical activities including walking during the last 7 days. In addition, the seventh question relates to the time that participants spend sitting during an average weekday. IPAQ is considered a reasonably valid measurement tool for measuring habitual physical activities based on a recent meta-analysis [25].

The Social Readjustment Rating Scale (SRRS) [26] and the Stress Response Inventory (SRI) [27] will be used to assess stress response at baseline and endpoint (visits 2, 14). SRRS is a very well-known 43 life events-list scale measuring stress that affects health based on a relative score. Subsequent validation has supported the links between stress and illness [28]; however, the scale has been criticized for its limited clinical utility. SRI includes emotional, somatic, cognitive, and behavioral stress responses and has a significantly high reliability and validity in clinical practice [27].

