The Fatigue Severity Scale (FSS) [29] will be used to assess fatigability at baseline, 2, 3, 4, 5, and 6 weeks, and endpoint (visits 2, 4, 6, 8, 10, 12, 14). FSS is the most commonly used 9-item self-report questionnaire to measure fatigue [30] and was validated as a simple and reliable instrument to assess and quantify fatigue for clinical and research purposes [31].

The Korean version of Beck’s Depression Inventory (BDI) [32] will be used to measure depressive symptoms at baseline and endpoint (visits 2, 14). BDI is a 21-item self-administered questionnaire with each item having a 0–3 response format and a maximum theoretical score of 63. The psychometric quality of this test is very good [33].

Urine samples will be measured at baseline and endpoint (visits 2, 14). Liquid chromatography quadrupole time-of-flight mass spectrometry-based nontargeted metabolomic analysis will be conducted with urine and serum samples.

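### Six secondary outcomes measured at seven visits rest on repeated-measures ANOVA with LOCF; the mixed model is optional with no trigger, and no test is named as deciding

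*Protocol article*

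**What the plan says.** All references are to the protocol article.

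- **Visits.** Under Secondary outcome measurements, body composition and waist and hip circumference are taken "at baseline, at 2, 3, 4, 5, and 6 weeks and endpoint (visits 2, 4, 6, 8, 10, 12, 14"). The Fatigue Severity Scale (FSS) follows the same schedule. A footnote to Table 1 places baseline just before the first treatment.
- **Repeated-measures method.** Under Statistical analysis: "Repeated measure analysis of variance (ANOVA) will be performed for the different time point assessments between groups and interaction between groups and observed time".
- **Mixed model.** The next sentence reads: "A mixed model approach will also be used if necessary". No criterion is given.
- **Missing data.** "We will apply the last observation carried forward (LOCF) analysis for ITT analysis". A per-protocol analysis is also planned, with no imputation rule of its own. The Sample size section allows for 20% dropout.
- **Other tests of the same outcomes.** A two-sample t-test compares primary and secondary variables between baseline and endpoint. Baseline adjustment is conditional: "Analysis of covariance (ANCOVA) will be used for adjustment of baseline characteristics if there is a possibility of covariance".
- **Primary lipids.** These are measured only "at baseline (visit 2) and endpoint (visit 14: within 3 days after completion of the 6-week treatment").

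**The concern.** The plan states a method for the seven-visit outcomes, and the method has three weaknesses.

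1. **Complete rows.** Classical repeated-measures ANOVA uses only women with a value at every visit. The intention-to-treat version therefore depends on LOCF, which freezes a woman's weight or waist at her last visit even if it was still changing. LOCF is stated for intention-to-treat only, so the per-protocol version would lose anyone with a missed visit. A likelihood-based mixed model uses the observed visits without either step, yet here it is only an optional extra.
2. **The group term.** If baseline is one of the seven time levels, the group main effect averages in a value taken before any treatment.
3. **No deciding test.** The main effect, the interaction, the t-test, a possible ANCOVA and a possible mixed model can each give a p-value for the same outcome, and nothing ranks them.

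These outcomes include the trial's only measures of weight, fat and girth, in a trial whose stated aim includes the efficacy of acupuncture for obesity.

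**Working it through.** **The plan's own figure.** The sample-size formula gives 2 × (1.96 + 0.84)² × 56.907² / 32.5² = 48.07, stated as 48 per arm, and 48 / (1 − 0.20) = 60 per arm. The figure reproduces. It concerns triglycerides and does not size the outcomes here; only n = 48 per arm and the 20% dropout are carried over.

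**Assumptions (not in the documents).** Unit SD at each visit; equal correlation ρ between visits, 0.8 to 0.95; baseline as a time level; complete data on 48 per arm; and two effect profiles over the seven equally spaced visits:

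- linear: 0, 1/6, 2/6, 3/6, 4/6, 5/6, 1
- constant after baseline: 0, 1, 1, 1, 1, 1, 1

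**Share of the visit-14 difference in the group main effect.** Linear: mean = 3.5/7 = 50%. Constant: 6/7 = 86%.

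**Reference difference.** Choose δ so that a baseline-adjusted visit-14 contrast has 80% power: δ = (1.96 + 0.84) × √[2(1 − ρ²)/48]. This gives δ = 0.343, 0.249 and 0.179 SD at ρ = 0.8, 0.9 and 0.95.

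**Power of the planned tests at that δ** (two-sided 0.05):

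- Main effect: z = share × δ / √[(2/48)(1 + 6ρ)/7]. At ρ = 0.8, linear: 0.5 × 0.343 / √(0.04167 × 0.8286) = 0.92, which is 15% power.
- Interaction, 6 df: noncentrality = (48/2) × δ² × SS / (1 − ρ), where SS is the sum of squares of the profile about its mean: 28/36 = 0.778 (linear) or 6/7 = 0.857 (constant). At ρ = 0.8, linear: 24 × 0.1177 × 0.778 / 0.2 = 11.0, which is 69% power by noncentral chi-square.
- t-test read as a change-score test: z = δ / √[(2/48) × 2(1 − ρ)]. At ρ = 0.8: 0.343 / √(0.04167 × 0.4) = 2.66, which is 76% power.

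| Test | ρ = 0.8 | ρ = 0.9 | ρ = 0.95 |
|---|---|---|---|
| Baseline-adjusted visit-14 contrast (set) | 80% | 80% | 80% |
| Group main effect, linear | 15% | 10% | 7% |
| Group main effect, constant | 35% | 20% | 12% |
| Group-by-time interaction, linear | 69% | 72% | 73% |
| Group-by-time interaction, constant | 74% | 77% | 78% |
| Change-score t-test | 76% | 78% | 79% |

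**LOCF.** Under the linear profile, a woman last seen at visit 8 carries forward a value that reflects 3/6 of the effect she would have shown at visit 14. The documents give no dropout pattern, so the overall bias cannot be sized.

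**The case against.** The strongest reply is that the plan already contains a sound test. The sentence that names the ANOVA also plans the interaction, which is the usual treatment test in that model and is not diluted. The t-test, read as a change-score test, loses only 1 to 4 percentage points against the proposed contrast and yields an endpoint difference. How baseline enters the model is a detail that an article may leave to an analysis plan. All of this stands. It limits the power argument to one term, but it does not supply a deciding test or remove the dependence on LOCF, both of which follow from what the text does say.

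Four stronger readings are tempting and are not supported:

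- **The stated method dilutes the treatment effect.** This is true of the group main effect only, and only if baseline is a time level. Baseline is listed among the seven assessments, which makes that likely, but its role in the model is not stated.
- **Missed visits remove a large share of women.** If 3% or 5% of values were missing independently at each of seven visits, 1 − 0.97⁷ = 19% or 1 − 0.95⁷ = 30% of women would have incomplete rows. These rates are assumed, and the loss does not apply to the intention-to-treat analysis, where LOCF fills the gaps.
- **The analyst may pick the model after seeing results.** The mixed model is worded as an addition to the ANOVA, and the statistician is blinded to allocation. This limits the risk, although the trigger remains undefined.
- **The trial's main conclusion is at stake.** The primary lipids have two time points, so the seven-visit issue does not reach them.

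**Conclusion.** The concern holds in limited form. As written, the intention-to-treat analysis of six secondary outcomes depends on LOCF with 20% dropout expected, the better-suited model is left to an undefined condition, and no test is named as deciding. The cost in power depends on which result is read: severe for the group main effect (7-35% where 80% is attainable), modest for the interaction (69-78%) and slight for a change-score t-test (76-79%). These figures rest on the assumed correlation, effect profiles, 48 complete women per arm and baseline as a time level; the ordering of the tests is the same across the range shown. The LOCF point does not depend on those power assumptions. This is a cheap improvement, not a threat to the primary analysis.

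**What to change.** For weight, fat mass, muscle mass, waist, hip and FSS, state one analysis:

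- a mixed model for repeated measures on visits 4 to 14, fitted by REML, with group, visit, group-by-visit and the baseline value as fixed effects;
- unstructured covariance, with a simpler structure named in advance in case of non-convergence;
- the visit-14 group contrast, with its confidence interval, as the single treatment test;
- no LOCF for these outcomes.

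The repeated-measures ANOVA and the t-test may stay only as labelled supportive analyses. The mixed model then no longer depends on an unstated condition.

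The cost is a change of wording, modest programming (the SPSS MIXED procedure can fit the model) and the need to specify the covariance fallback. The model still assumes that data are missing at random given the observed visits. That is an assumption too, but it does not hold a woman's value fixed after she leaves.
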